#### Hypothesis

For this part of the project, we hypothesize that the 'five steps to quit' intervention (with or without offering the therapeutic option) will be more effective and cost-effective in getting people who are suspected of tuberculosis to quit nicotine use and remain quitters at both 4 weeks and six months after the treatment compared to usual care and information leaflet.

#### Settings

The study will be conducted in health centres in the public sector which are designated TB diagnostic centres (as per WHO's definition) in rural and urban settings in two districts in Punjab, Pakistan. This has been the setting of a number of research activities carried out by the investigating team over the last 12 years mainly in tuberculosis. Diagnostic centres, in a typical district in Punjab, are generally:

• Rural health centres - rural settings

• Tehsil headquarter hospitals - urban settings

Centres are typically staffed by one to three doctors, nursing staff, laboratory technician, pharmacist and community health workers. They are also equipped with a basic microbiology laboratory capable of examining sputum for AFB. The outpatient departments are open to the population of the catchment area including referrals from Basic Health Units (a single doctor manned primary care health centre). Patients with suspected tuberculosis once seen are screened with two/three sputum examinations. If diagnosed with TB, they are registered and commenced on anti-tuberculosis therapy.

#### Study Design

To deliver 'five steps to quit' intervention (with or without offering the therapeutic option), individual patients cannot be randomised to the intervention and control arms within health centres due to the possibility of contamination. The most suitable design to assess its effectiveness is a cluster randomised controlled trial (RCT). The overall design is summarised in the trial flow chart in Figure 1. We propose to have three arms in the trial: (a) control arm - usual care and an information leaflet; (b) intervention arm 1 - 'five steps to quit' that includes offering therapeutic option; and (c) intervention arm 2 - 'five steps to quit' that excludes therapeutic option). We propose to select a total of 33 diagnostic centres (11 at each control and the two intervention arms) and to recruit 50 patients with suspected tuberculosis (see the section on sample size below).

**Figure 1 F1:**
[figure not shown]
**Trial flow chart**.

#### Participants and Sampling

The sampling frame will consist of all TB diagnostic health centres that are approached for this study and their doctors and other paramedical staff have expressed willingness to participate. Access to these diagnostic centres will be facilitated by one of the investigating partner organisations, ASD, which has been given the responsibility of implementing the DOTS strategy in 18 districts in Punjab. Health centres in the sampling frame will be stratified according to rural (RHC) and urban location (THQ). 11 health centres will be randomly allocated to each of the two intervention arm and the control arms, using computer generated random number lists by an independent scientist.

In each health centre, we will approach adult patients (≥18 years), who cough for 3 or more weeks and are therefore suspected and screened for pulmonary tuberculosis. We would aim to recruit at least 50 patients from each centre over a period of three to six months. Patients will be provided with both verbal and written information about the study and only those who consent will be recruited in the study.

Patients whose condition requires hospital admission or other urgent medical attention will be excluded. Patients will be approached and recruited each day.

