#### Sample size

We have estimated a sample size of 33 clusters (diagnostic centres) 11 in each arm of the trial. Each cluster size will be 40. The actual number of patients recruited in each cluster will be 50 patients with suspected tuberculosis each [assuming 80% will complete the trial up to the review at 6 months as per study in Sudan[24]] to give 80% power to detect a difference in quit rates of 20% in the intervention arm compared with 10% in the control arm. The value of α is set at 0.05. The assumptions underlying this estimation are:

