##### Attrition Rates

The sample size calculation incorporates an attrition rate of 20%. This is based on the observations made in the trial of tobacco control in TB patients in Sudan where less than 20% patients defaulted over a period of six months. An intention to treat analysis will account for any non-differential loss to follow up. As part of DOTS, patients with diagnosed TB are generally followed up for a period of six months. However, follow up of non-TB patients will be arranged as part of the trial.

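### The centres come from two districts but allocation is stratified by rural/urban only, so district balance across arms of 11 centres is left to chance: a cheap improvement, not a bias

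*Protocol article*

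**What the plan says.** Under Objective 3, Settings, the protocol article places the trial "in rural and urban settings in two districts in Punjab, Pakistan". Under Participants and Sampling it names one stratification factor: "Health centres in the sampling frame will be stratified according to rural (RHC) and urban location (THQ"). It then states that "11 health centres will be randomly allocated to each of the two intervention arm and the control arms, using computer generated random number lists", the lists being produced by an independent scientist. District is not mentioned in the allocation.

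The Sample size section gives the scale: "We have estimated a sample size of 33 clusters (diagnostic centres) 11 in each arm of the trial", with "Each cluster size will be 40" after 20% attrition from 50 recruited, "to give 80% power to detect a difference in quit rates of 20% in the intervention arm compared with 10% in the control arm". The Intra-cluster variation section takes an ICC of 0.036 from UK primary care trials.

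The Data analysis section describes an intention-to-treat comparison of abstinence between arms. It names no model and no covariates, so it neither includes nor excludes a district term. Nowhere does the article give the number of centres per district, the rural/urban numbers, or any difference between the districts in quit rates.

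**The concern.** The stratification factors must be settled before the list is drawn. A later analysis plan can add a district term but cannot restore balance. With 11 centres per arm, a two-level centre characteristic that is not controlled will often be uneven between arms.

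If quit rates or follow-up differ between the districts, an uneven split moves an unadjusted intervention-control difference in whichever direction chance dictates, and it invites argument over the result. A factor known in advance also offers some precision, which is worth having in a trial with few clusters.

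**Working it through.** **1. The plan's own figure.** The inputs are 20% v 10%, "The value of α is set at 0.05" (taken as two-sided), 80% power and ICC 0.036. Individual randomisation needs 199 per arm.

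- With 40 per cluster, the design effect is 1 + 39 × 0.036 = 2.404. Then 199 × 2.404 = 478 per arm, and 478/40 = 11.96 clusters.
- Eleven clusters of 40 (440 per arm) give 76.6% power.
- With 50 per cluster, the design effect is 1 + 49 × 0.036 = 2.764. Then 199 × 2.764 = 550 per arm, or 11.0 clusters, with 80.0% power.

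The stated 11 therefore matches the recruited size, not the analysed size of 40. That is a separate matter. It matters here only because the baseline below is about 76%, not 80%.

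**2. Chance of district imbalance.** Let D of the 33 centres lie in one district. Under random 11/11/11 allocation, the numbers (a, b, c) from that district in the three arms have probability

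C(11,a) × C(11,b) × C(11,c) / C(33,D), with a + b + c = D.

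Summing over the relevant cells, for three assumed splits:

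| Split | One given pair, gap ≥2 | One given pair, gap ≥3 | One given pair, gap ≥4 | At least one contrast with control, gap ≥3 |
|---|---|---|---|---|
| 17/16 | 53% | 29% | 14% | 48% |
| 22/11 | 51% | 27% | 12% | 44% |
| 25/8 | 47% | 22% | 8% | 37% |

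This ignores the rural/urban strata. Simulation with them in place (rural/urban 21/12, 24/9 or 18/15, with 16 centres in one district) gives about 53% for a gap of 2 or more in one pair, 30% for 3 or more and 15% for 4 or more. The existing stratum does not protect district balance.

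**3. Size of the shift.** For a difference d between districts and a gap of k centres, an unadjusted contrast moves by d × k/11. With d = 5 points (assumed), k = 2 gives 0.9 points and k = 3 gives 5 × 3/11 = 1.4 points. The planned difference is 10 points.

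**4. Standard error and power.** Variance of a centre mean at an average quit rate of 0.15 with 40 analysed:

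- between centres: 0.036 × 0.15 × 0.85 = 0.00459
- within centres: 0.964 × 0.15 × 0.85 / 40 = 0.00307
- total: 0.00766

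The standard error of an arm difference is √(2 × 0.00766/11) = 0.037, or 3.7 points. The 1.4-point shift is 1.4/3.7, just under 0.4 of a standard error. Power is Φ(0.10/0.0373 − 1.96) = Φ(0.72) = 76.4%.

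A 5-point gap between two equal districts contributes (0.05/2)² = 0.000625, which is 8.2% of the total. Removing it leaves 0.00704, a standard error of 3.58 points and power Φ(0.10/0.0358 − 1.96) = Φ(0.84) = 79.8%.

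**5. Where the gain comes from.** Adjusting for district without stratifying costs about 4% in variance on average, because arm and district are then partly confounded. The variance becomes 0.00704 × 1.04 = 0.0073, the standard error 3.64 points and power about 78.4%. So the model term alone yields about 2 of the 3.4 points, and stratification adds the rest.

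**6. Range.** If district accounts for 0, 10, 25 or 50% of the between-centre variance, removing it gives power of 76.6, 79.1, 82.9 or 89.2% with 40 per cluster (design-effect formula of step 1). At a 15% mean quit rate, the last three shares correspond to district gaps of about 4.3, 6.8 and 9.6 points. With no district difference, the lost degree of freedom lowers power by about 0.1 point.

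**The case against.** The case for leaving the plan alone is fair. Rural/urban is a sensible factor, because the two strata are different types of facility, and one stratifier for 33 clusters in three arms is ordinary practice. Nothing in the article promises district balance, so nothing is contradicted. The two inputs that drive the size, the district split and the 5-point gap, are assumptions. Even then, the shift from a 3-centre gap is under 0.4 of a standard error. All of this stands, and it keeps the point small.

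A reader might infer three stronger things that the document does not support.

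- **That the result would be biased.** It would not. Allocation is random, and chance imbalance is part of the random error that the standard error describes.
- **That district variation necessarily stays in the error.** That depends on the analysis model, which Data analysis leaves open and an analysis plan may fix. A district term recovers most of the precision without stratification.
- **That district variation adds to the error already planned for.** The calculation above treats it as part of the between-centre variance implied by the ICC, so counting it again would be double counting. The shortfall from 80% to about 76% comes from the cluster-size figures and has nothing to do with district.

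What survives is that the allocation factors are fixed here, before randomisation, and that a known factor can be balanced at almost no cost.

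**Conclusion.** The point holds as a low-severity design improvement. With two districts and rural/urban as the only stratifier, a gap of 2 or more centres between a given pair of arms is about as likely as not (47% to 53% over the splits tried). A gap of 3 or more occurs in 22% to 29% of single contrasts, and in 37% to 48% for at least one contrast with control. A gap of 4 or more in one given pair is uncommon, at 8% to 15%.

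The consequence is conditional. It needs a real district difference, for which the article gives no evidence. At an assumed 5 points, the benefit of accounting for district is about 3 points of power. At zero there is none.

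**What to change.** Before the list is drawn, allocate within district as well as rural/urban. Four strata and three arms will not generally divide evenly, so use constrained randomisation, or carry incomplete blocks across strata, to keep 11 centres per arm. State the number of centres per district and stratum. Include district and rural/urban as terms in the comparison of abstinence, so that the analysis matches the allocation.

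The cost is a revised allocation list and one more model term. The drawbacks are urban strata that may be small and not divisible by three, and one degree of freedom for district (about 0.1 point of power if the districts do not differ). If the list has already been drawn, the model term alone recovers most of the possible gain, provided it is specified before outcomes are seen.

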#### Delivery of the intervention

We propose to use a systematic, standardised approach to deliver 'five steps to quit' to make it effective and equitable[30]. It is envisaged that the intervention will be primary delivered by the TB DOTS facilitator based in the diagnostic centre with the help and under the supervision of the primary care doctor (Table 1). He will assess patients' eligibility for the study and send them to the TB DOTS facilitator for further assessment. All eligible patients will be provided with verbal and written information about the study and invited to participate. Patients who agree to take part will be taken through different components of the 'five steps to quit' programme in two appointments. Patients in intervention arm 1 will also be offered therapeutic option (Bupropion) and such patients will be referred to the primary care doctor for assessing suitability and prescribing Bupropion.

**Table 1 T1:** Follow up and contacts with health professionals

Trial arms	First contact	FU at week 1	FU at week 5	FU at week 8	FU at week 25
Intervention 1 (brief psychological intervention + therapeutics)	Assess eligibility at the laboratory	TB DOTS facilitator	TB DOTS facilitator	TB DOTS facilitator	TB DOTS facilitator
	TB DOTS facilitator	Doctor	Doctor (if necessary)		
	Doctor				
Intervention 2 (brief psychological intervention only)	Recruitment at the laboratory	TB DOTS facilitator	TB DOTS facilitator		TB DOTS facilitator
	TB DOTS facilitator				
Control (usual care + leaflet)	Recruitment at the laboratory	TB DOTS facilitator	TB DOTS facilitator		TB DOTS facilitator
	TB DOTS facilitator				

The TB DOTS facilitators and primary care doctors will be given a training course (using training manual) on the "five steps to quit" programme on the use of desk-guide and focusing on[30]:

• The scientific basis of the intervention

• Techniques to enquire about the status of tobacco use

• Providing brief advice on the benefits of stopping its use through visual images

• Approaches to assess nicotine dependence and motivation to quit

• Using this motivation to propose various treatment options explaining their pros and cons

• Training in the use of available pharmacotherapies and other cognitive-behavioural strategies

• The procedure for follow-up and other technical and organisational aspects.

• Familiarity with the recording and reporting system such as revised records and new tools

Training of TB DOTS facilitators will also focus on the brief counselling techniques based on cognitive-behavioural model[32]. A simple desk-guide will be provided with simple algorithms and instructions for health professionals to follow "five steps to quit" programme. This will also include glossy images to support patients in understanding the benefits of stopping smoking. The TB DOTS facilitator, for all eligible patients, will be responsible for:

• Assessment of the status of their tobacco use through a checklist of questions

• Advising on benefits of quitting using visual and written educational material

• Assessment of willingness for inclusion in the study and motivation to quit using a simple scoring card

• Registration and recording of demographics and contact details

• Structured counselling using a desk guide and patient planner

• Giving a quit date after a week

On the subsequent visit in a week's time, TB DOTS facilitator will be responsible for

• assessing the status of their tobacco use

• Sharing their experience of attempting to quit, listen to the difficulties they had and providing supportive counselling to help cope with the difficulties

• Referring them to doctor if the intervention arm includes therapeutic option

• Arranging follow up in a month's time.

At follow ups at week 5 and 25, TB DOTS facilitators will be responsible for

• Reassessing status of nicotine use and recording it in the tobacco use questionnaire/register

• Reviewing treatment and other options

• Rearranging follow up as per desktop guide.

In the intervention arm 1, the primary care doctors, in addition to supervising TB DOTS facilitators, will be responsible for assessing and prescribing therapeutics (Bupropion) to patients who wish to quit and are being referred by the TB DOTS facilitators. All patients on treatment will have an additional follow up visit at week 8. In intervention arm 2, doctors will be only responsible for supervising TB DOTS facilitators. They will be provided with the appropriate training and relevant materials.

Apart from the relevant training and materials, health professionals will not be provided with any other incentive, financial or otherwise. However, treatments packs will be provided from the research budget. The research officer will also organise regular supervisory visits to oversee patient management and data collection procedures. Monthly cluster meetings of the health professionals involved will also be organised to discuss progress and potential problems.

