### Treating tobacco dependence

It has been suggested that at least 180 million deaths related to tobacco can be avoided by reducing current tobacco consumption by 50%. Surveys suggest that three out of four smokers wish to quit and one-third attempt to quit every year[6]. However, only 1-3% are successful if attempting on their own[7]. There is overwhelming evidence for the effectiveness and cost-effectiveness of a number of psychological and pharmacological treatments for tobacco dependence[8,9]. The evidence suggests that both behavioural and pharmacological therapies have the potential to double the quit rates among smokers and are highly cost-effective[10]. In low and middle-income countries, spontaneous quit rates are lower suggesting an even greater need for supporting people who wish to quit, and an opportunity to have a higher health benefit.

One of the several challenges in treating tobacco addiction in low- and middle-income countries is the lack of resources and governmental funding for the implementation of effective interventions. Many countries facing a tobacco epidemic are also confronting other challenges related to communicable diseases and nutrition-related disorders. Therefore, it may not be possible for countries with limited resources to shift priorities. However, existing programmes (such as TB control) can be utilised to extend their role to tobacco control with minimum investment. The WHO recommends integration of such tobacco cessation interventions into an overall policy on tobacco control and incorporation of these programmes into general health care[8].

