#### The Control Arm

Participants in the control arm will also be recruited from those who are suspected of TB and screened using sputum examinations. The changes in the relevant registers will be made to record the status of nicotine use and health professionals will be given instructions on recording it on-site. The TB DOTS facilitators in control diagnostic centres will be provided with patient education leaflets to be given out to all patients recruited in the study. Apart from recording their status of nicotine use and arranging follow up at week 1 and 5, they will be provided usual care. No other components of the intervention will be delivered. We do not anticipate a significant risk of contamination, i.e. patients moving from one diagnostic centre to another, due to the geographical spread of facilities, and because no publicity will be produced regarding the availability of the treatment package in other facilities. In addition, we do not anticipate a significant benefit (other than what has been recorded previously in controls) in the control arm given that asking about nicotine use and providing information leaflets, are not, by themselves, sufficient to lead to stopping nicotine use.

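### The enrolment step is described inconsistently and differently by arm, and tobacco use is not an entry criterion, so arms could enrol different patients

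*Protocol article*

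**What the plan says.** **Who can enter.** Under Participants and Sampling, centres are stratified and randomly allocated. Then, "In each health centre, we will approach adult patients (≥18 years), who cough for 3 or more weeks and are therefore suspected and screened" (the screening is for pulmonary TB). The exclusion is: "Patients whose condition requires hospital admission or other urgent medical attention will be excluded". Only those who consent are recruited. Tobacco use is neither an inclusion nor an exclusion criterion.

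**Enrolment in intervention centres.** Delivery of the intervention gives two accounts.
- The opening paragraph says eligible patients are informed and invited, and then: "Patients who agree to take part will be taken through different components" of the programme.
- The later list of facilitator duties, which applies to all eligible patients, runs: tobacco status, advice on the benefits of quitting, "Assessment of willingness for inclusion in the study and motivation to quit using a simple scoring card", registration, counselling, quit date.

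**Enrolment in control centres.** Controls also come from patients screened for TB. "Apart from recording their status of nicotine use and arranging follow up at week 1 and 5, they will be provided usual care". They receive a leaflet once recruited, and no other intervention component. No advice or motivation step is described before inclusion.

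**Table 1.** The first-contact cell for arm 1 reads "Assess eligibility at the laboratory". For arm 2 and control it speaks instead of recruitment at the laboratory.

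**Outcome and analysis.** Under Outcomes, abstinence is a proportion of trial participants. Under Data analysis, the comparison is by intention to treat.

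**The concern.** In a cluster trial that enrols patients after allocation, randomising centres does not by itself make the patients comparable. They are comparable only if each arm enrols by the same steps. Staff in intervention centres are trained in the programme and so know their arm. If they advise a patient and gauge motivation before settling inclusion, while control staff simply recruit, the intervention arms may hold more patients who are ready to quit. Such patients quit more often under any care, and intention to treat protects only those already enrolled.

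The missing tobacco criterion is a second route. A non-user who is enrolled and counted as abstinent adds to the numerator of the quit rate. If the arms enrol non-users in different proportions, the rates differ for a reason unrelated to treatment.

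**Working it through.** The plan gives no figure for selection, so the size can only be illustrated.

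**Inputs from the protocol**
- Control quit rate 10%, planned intervention rate 20% (Quit rates).
- 11 centres per arm, 40 analysed per centre, α = 0.05 (Sample size). Sidedness is not stated; two-sided is assumed here.
- ICC 0.036 (Intra-cluster variation).
- Surveys suggest that "three out of four smokers wish to quit" (Treating tobacco dependence).

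**Effective sample size, one intervention arm against control**
- Analysed per arm: 11 × 40 = 440.
- Design effect: 1 + (40 − 1) × 0.036 = 2.404.
- Effective n per arm: 440 / 2.404 = 183.

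On these inputs the planned 10-point difference has 76.6% power rather than the stated 80%. That is a separate matter and does not affect this point.

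**Worst case for motivation, with no treatment effect.** Assume intervention centres enrol only the 75% who wish to quit, control centres enrol everyone, and all quitting occurs among those who wish to.
- Intervention quit rate: 0.10 / 0.75 = 0.133.
- Spurious difference: 0.133 − 0.100 = 0.033, a third of the planned 10 points.
- SE: √[(0.133 × 0.867 + 0.10 × 0.90) / 183] = 0.0335.
- Probability that a two-sided 5% test rejects: about 0.17.

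**Milder cases, with no treatment effect.** These assumptions are not in the protocol: half of controls are motivated, and 80% of intervention patients are.
- Motivated patients quit twice as often. Unmotivated rate: 0.10 / (0.5 × 2 + 0.5) = 0.067. Motivated rate: 0.133. Intervention rate: 0.8 × 0.133 + 0.2 × 0.067 = 0.120. Rejection: 9%.
- Motivated patients quit five times as often. Rates: 0.033 and 0.167. Intervention rate: 0.8 × 0.167 + 0.2 × 0.033 = 0.140. Rejection: 22%.
- Equal mix in both arms: rejection 5%, as it should be.

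**Non-users counted as abstinent, with no treatment effect**

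| Non-users in one arm | Non-users in the other | Rates | Rejection |
|---|---|---|---|
| 5% | 0% | 0.95 × 0.10 + 0.05 = 14.5% vs 10% | 26% |
| 10% | 0% | 0.90 × 0.10 + 0.10 = 19.0% vs 10% | 69% |
| 10% | 10% | 19.0% vs 19.0% | 5% |

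The distortion needs an imbalance, and it can favour either arm. The imbalances shown are assumed.

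**The case against.** The case on the other side is substantial, and it rules out several stronger readings.

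- **That intervention centres select on motivation.** A reader might infer this from the shared bullet. But the bullets are a list of responsibilities, not a stated sequence, and no threshold is given. The Intervention and its key components uses motivation to judge suitability for treatment options, and bupropion is limited to patients who want to quit, which would be redundant if only they were enrolled. Against this, Outcomes counts users who decide to quit and are registered, and the pilot fills in a card for each user willing to try. That registration is for the programme, however, and need not be trial enrolment.
- **That advice certainly precedes consent.** The text that does state an order puts agreement first. What stands is that two parts of one section disagree, and a centre could follow either.
- **That controls get no advice and no motivation score.** They get a leaflet after recruitment, and the patient leaflets are described as including advice on stopping. The questionnaire under Data collection records motivation and is not restricted by arm. What stands is that nothing says controls are scored before inclusion.
- **That Table 1 separates intervention from control.** It does not. Arm 2 is worded like control, and only arm 1 differs.
- **That the missing tobacco criterion in itself biases the comparison.** It applies to every arm and biases only if non-users are unevenly enrolled. The intention to study tobacco users is plain elsewhere, and the flow chart, which is not shown, may say so. The written criteria still should.
- **That 17% is the expected error rate.** It takes total exclusion in one arm and none in the other. The 75% describes smokers in surveys, not TB suspects, and controls must also consent, so they are not all comers.

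**Conclusion.** The concern holds as an inconsistency that leaves room for recruitment bias; the documents do not show that biased selection is planned. Enrolment follows allocation, the accounts of when inclusion happens conflict, the step before inclusion is described differently for intervention and control centres, and the criteria do not tie the outcome's denominator to tobacco users.

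If the duty list were followed as written, the likely direction for motivation favours the intervention. For non-users it could go either way. The size is unknown: 13.3% against 10%, with about 17% false positives, is a worst-case illustration for motivation under the survey figure, and the other figures rest on assumed mixes. The change is worth making because differential enrolment cannot be fully repaired in the analysis. Confidence is medium, since the condensed article and the missing flow chart leave some doubt about what centres will actually do.

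**What to change.** 1. Add current tobacco use to the criteria under Participants and Sampling.
2. Reconcile the two accounts in Delivery of the intervention with the first-contact cells of Table 1, so that all three arms use the same enrolment step: tobacco status, daily amount, consent. Place it before any advice, and state that enrolment does not depend on the motivation score.
3. Record baseline motivation with the existing questionnaire at the same point in all arms. It should precede advice, because a score taken after advice may already reflect the intervention. Assessing motivation is one of the five steps, so The Control Arm must be amended to allow it.
4. Optionally, adjust the main comparison for baseline motivation and daily use. This supplements a common enrolment step and does not replace it.

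The cost is protocol wording and use of an existing form in control centres. The drawback is that asking controls about motivation may prompt a few of them to quit, which would slightly narrow the contrast.
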